**Protocol Number:** 818540

**Principal Investigator:** [name]

**Protocol Title:** Implementation of Prolonged Exposure in the Army: Is consultation necessary for effective dissemination?

**Short Title:** The Post-Traumatic Stress (PTS) Study

**Protocol Description:** This study will examine whether Prolonged Exposure (PE) for posttraumatic stress disorder (PTSD) can be successfully disseminated and implemented in the Army. 120 mental health providers will attend a 4-day PE workshop and will receive in-depth case consultation or no additional consultation following the workshop. Providers will complete surveys about their therapy practices. Patients seeking care for PTSD from providers will be recruited and consented to assess treatment response.

**1.5. Disclosure of Significant Financial Interests***

*Does any person who is responsible for the design, conduct, or reporting of this research protocol have a FINANCIAL INTEREST?*

No

**Certification**

*I have reviewed the Financial Disclosure and Presumptively Prohibited Conflicts for Faculty Participating in Clinical Trials and the Financial Disclosure Policy for Research and Sponsored Projects with all persons who are responsible for the design, conduct, or reporting of this research; and all required Disclosures have been attached to this application.*

Yes

**2. Study Instruments**

*2.1. Provider Measures*

Provider Demographics & Background Survey: The Provider Demographics Form assesses standard demographics (ethnicity, gender, age, etc.) and professional information (e.g., military rank, type of schooling, etc.). It also includes items designed to assess providers training, theoretical orientation and experience providing evidence-based treatments, including their knowledge of PE, experience with PE, and attitudes towards PE. This measure will be completed by providers in both conditions.

Provider Measure of Attitudes: This is a 59-item measure of current treatment practices (7 items), beliefs about the effectiveness of PE (1 item), self-confidence in delivering PE (8 items), and perceptions about patient factors that would influence providers decision to use PE (22 items). In addition, this measure includes an embedded, modified version of the 21-item Therapist Beliefs about Exposure Scale (TBES; Deacon et al, 2013). All TBES items were modified to refer to PE specifically, rather than exposure therapy which is a more general term. The TBES has strong psychometric properties including excellent internal consistency ( = .90-.96), high test-retest reliability (r = .89; Deacon et al., 2013). The Provider Measure of Attitudes will be completed by providers in both conditions prior to attending the PE training workshop, after attending the PE training workshop, and at regular 3-month intervals over the course of 18 months following the completion of training (i.e. for providers in the standard condition, after the completion of the training workshop; for providers in the extended condition, after the completion of two supervised PE training cases).

Procedures Used in Treatment Checklist: This 4-item form is meant to collect data on what treatment techniques providers used during their sessions with study patients. Providers will also use the form to record patients’ biweekly PCL and PHQ-9 scores.

*2.2. Patient Measures*

Patient Demographics: The Patient Demographics Form assesses standard demographics (ethnicity, gender, age, etc.).

The Mini International Neuropsychiatric Interview (M.I.N.I.; Sheehan et al., 1998): The M.I.N.I. is a 30 minute diagnostic structured interview for 17 Diagnostic and Statistical Manual (DSM)-IV Axis I psychiatric disorders, including mood disorders, anxiety disorders, and substance use disorders. This instrument has been used in numerous studies of veteran samples (e.g., Kashdan, Frueh, Knapp, Hebert, & Magruder, 2006; Magruder et al., 2005; Stecker, Fortnery, Hamilton, & Ajzen, 2007). The complete M.I.N.I. will be administered and used to assess, in a standardized way, for evidence of any psychotic disorder that would exclude participants from treatment on this study.

The Clinician Administered PTSD Scale for DSM 5 (CAPS 5; Weathers, Blake, Schnurr, Kaloupek, Marx, & Keane, 2012): The CAPS is a 30-item structured interview that can be used to: 1) make current (past month diagnosis of PTSD; 2) make lifetime diagnosis of PTSD; and 3) assess PTSD symptoms over the past week. The CAPS interview yields a total symptom severity score and symptom cluster severity scores. In addition to assessing the 20 DSM-5 PTSD symptoms, questions target the onset and duration of symptoms, subjective distress, impact of symptoms on social and occupational functioning, improvement in symptoms since a previous CAPS administration, overall response validity, overall PTSD severity, and specifications for the dissociative subtype (depersonalization and derealization). For each symptom, standardized questions and probes are provided. The CAPS was designed to be administered by clinicians and clinical researchers who have a working knowledge of PTSD, but can also be administered by appropriately trained paraprofessionals. The CAPS takes 30-45 minutes to administer.

The CAPS assumes that an index trauma has already been identified by another means (e.g., by using a trauma checklist or structured interview questions) and does not include any questions to identify the index trauma. Thus, prior to administration of the CAPS, the assessor will ask the patient three questions in order to identify the index trauma. These three-questions are referred to as the Trauma Screen and will be administered at the first assessment only. At the second assessment, patients will complete a single question (Trauma Check) to confirm whether the previously identified index trauma was a major focus of his/her treatment.

Beck Scale for Suicidal Ideation (BSSI; Beck, Kovacs, & Weissman, 1979): The self-report version of the BSSI was will be used to evaluate the current intensity of the participants specific attitudes, behaviors, and plans to commit suicide. The BSSI has high internal consistency and strong concurrent validity with the clinician-administered version for both inpatients and outpatients (Beck, Brown, & Steer, 1997). This measure has been used in many studies of veteran populations (e.g., Bell & Nye, 2007; Cigrang et al., 2011; Koons et al., 2001). The original 21-item self-report requires that the patient fill out Part 2 (items 6-20) only if he/she previously endorsed items 4 or 5.

PTSD Checklist Civilian Version (PCL-C; Weathers et al., 1991): The PCL-C is a 17 item self-report measure that evaluates how much participants have been bothered by key PTSD symptoms in the past month. Patients will be asked to complete this measure, the PCL-5, or whichever PTSD measure is used as part of routine clinical care every two weeks, and their total score will be collected by the provider and listed on the Procedures Used in Treatment Checklist.

PTSD Checklist-5 (PCL-5; Weathers et al., 2013): The PCL-5 is a 20 item self-report measure that assesses/corresponds to the 20 DSM-V symptoms of PTSD, updated from the original PCL. Patients will be asked to complete this measure, the PCL-C, or whichever PTSD measure is used as part of routine clinical care every two weeks, and their total score will be collected by the provider and listed on the Procedures Used in Treatment Checklist.

Patient Health Questionnaire -9 (PHQ-9; Pfizer, 1999): The PHQ-9 is a commonly used self-report measure of depression that consists of 9 items that assess depressive symptoms. Each item is composed of four statements that reflect symptoms severity. The PHQ-9 has internal reliability of .89 and .86. It does correlate strongly with other measures of depression. (Huang, Chung, Kroenke, Deluded & Spitzer, 2005). The PHQ-9 has been used in numerous studies of military personnel. Patients will be asked to complete the PHQ-9 every two weeks, and their total score will be collected by the provider and listed on the Procedures Used in Treatment Checklist.

The State-Trait Anger Expression Inventory-2 (STAXI-2; Spielberger, 1999): The STAXI-2 is a 57-item inventory which measures the intensity of anger as an emotional state (State Anger) and the disposition to experience angry feelings as a personality trait (Trait Anger). The instrument consists of six scales measuring the intensity of anger and the disposition to experience angry feelings. Items consist of 4-point scales that assess intensity of anger at a particular moment and the frequency of anger experience, expression, and control. Only the State Anger subscale will be used in this study.

Alcohol Use Disorder Identification Test (AUDIT; Allen, Litten, Fertig, & Barbor, 1997): The AUDIT is a 10-item measure of at-risk alcohol use that has been widely used in studies of veterans (e.g., Bradley, McDonell, Kivlahan, Diehr, & Fihn, 1998; Bush, Kivlahan, McDonell, Fihn, & Bradley, 1998; Morton, Jones, & Manganaro, 1996). Items assess the quantity and frequency of drinking as well as the consequences associated with drinking. The maximum total score is 40, and a cut-off score of 8 or more has been shown to have a sensitivity and specificity of 96% in detecting at-risk alcohol use.

Credibility/ Expectancy Questionnaire Post-Treatment Survey (CEQ; Devilly & Borkovec, 2000): The CEQ Post-Treatment Survey is a 6-item measure of treatment expectancy and rationale credibility. Each item is rated on a 9- point scale (1= not at all, 9= extremely). The measure has demonstrated high internal consistency and good test-retest reliability (Devilly & Borkovec, 2000). The CEQ Post-Treatment Survey will be administered at the second assessment.

Client Satisfaction (CSQ; Larsen, Attkisson, Hargreaves, & Nguyen, 1979): This 8-item questionnaire measures satisfaction with treatment services received. Items are rated on a 4-point Likert scale, from 1 (excellent) to 4 (poor) with higher scores indicating less satisfaction. It has high internal consistency and is correlated with treatment completion, number of therapy sessions attended, and change in client-report symptoms (Attkisson et al., 1982). This will be given at the second assessment.

Additional Services Form (ASF): The Additional Services Form is a clinician-administered interview which includes 9 items in the First Assessment and 10 items in the Second Assessment. It assesses whether the patient had applied or intend to apply for military disability services. It also assesses patient participation in concurrent mental health services. This measure will be used to assess and control for additional mental health services or anticipated medical board review among patient-participants.

**2.3. Group Modifications**

There will not be any modifications to any study instruments for different groups. However, only the Extended PE training condition will complete the Provider Post-Consultation Measure of Attitudes because they will be the only group that receives consultation.

**2.4. Method for Assigning Subjects to Groups**

The study proposes to enroll approximately 100 participants in each condition. Participants will be randomized to conditions by a computer-based random list generator.

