**6. Study Design**

**Phase***

Not applicable

*6.1. Design*

This is a randomized clinical trial comparing two methods of training mental health providers in Prolonged Exposure (PE) treatment for Posttraumatic Stress Disorder (PTSD). Two hundred (200) mental health providers at three medium-to-large CONUS Army installations will be randomly assigned to either Standard PE training or Extended PE training. All providers will receive a 4-day PE workshop, along with the distribution of training materials and treatment manuals, conducted at the military site by the Overall Study PI, [name], and her team. Following the 4-day workshop, participants randomized to the Extended PE training will receive weekly phone consultation with a PE expert on two PE therapy clinical cases followed by twice monthly telephone consultation as needed for six months. Participants randomized to the Standard PE training group will not receive any additional consultation following the workshop. Providers will not be required to use PE therapy to treat their patients with PTSD; using PE will be optional. A major outcome of this study is the proportion of the providers PTSD patients that are offered PE. The mental health outcomes of providers PTSD patients will also be monitored as a second major outcome. Patients seeking care for PTSD from participating providers will be recruited, consented and offered treatment for PTSD and related problems to prospectively and systematically assess what type of treatment they are offered and their response to treatment.

*6.2. Study duration*

The study is expected to start in May 2014 and end in May 2017. Subject recruitment and data collection will mostly occur in years 2, 3, and 4. Data analysis will occur in year 4.

*6.3. Resources necessary for human research protection*

Describe research staff and justify that the staff are adequate in number and qualifications to conduct the research. Describe how you will ensure that all staff assisting with the research are adequately informed about the protocol and their research related duties. Describe access to a population that would allow recruitment of the targeted number of subjects. If medical or psychological services as a consequence of the research, describe how the subject will be referred to those services. Describe your facilities and justify that the facilities are adequate. Verify that there is sufficient time to conduct and complete the research.

*6.4. Research Staff*

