**8. Study Procedures**

*8.1. Procedures*

This is a randomized clinical trial comparing two methods of training in Prolonged Exposure (PE) treatment. Consented mental health providers at three medium-to-large Continental United States (CONUS) Army installations will be randomly assigned to either implement Standard PE training or Extended PE training. Mental health providers at three military installations will be invited to participate in a 4-day PE workshop which will be conducted at the military site by PE experts from the University of Pennsylvania’s Center for the Treatment and Study of Anxiety. The PE expert conducting the workshop were trained by and work closely with [name], the developer of PE and one of the world’s leading experts in PTSD and PTSD treatment. As part of the PE workshop, the provider will receive training materials and treatment manuals. Following enrollment in the study, provider-participants will also receive an email/letter from the PI, [name], thanking them for their study participation. Following the 4-day workshop, participants randomized to the Extended PE training will receive weekly case consultation from PE experts on two PE training cases including the review of video-tapes made of their two supervised cases. Patient consent to these video-recordings of clinical care will be accomplished by each sites local form for recording of patient care. These training case patients are not considered study participants. Provider will obtain consent from their patients to video-record using a separate clinical consent document. The video-recordings of the training cases will be copied onto DVD at the individual performance sites, labeled with the providers study number, and mailed directly to the University of Pennsylvania Center for the Treatment of Anxiety for review as part of case consultation teleconferences using an express service (e.g., FedEx) and tracked for receipt.

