Participants randomized to the Standard PE training group will not receive any additional consultation following the workshop. In addition to mental health providers, patients seeking treatment from participating providers will be recruited and consented to examine their symptoms of PTSD and related problems during treatment. Providers will not be required to use PE therapy to treat their patients with PTSD; rather it will be an option for treatment. A diagnostic feedback form will be given to the provider by the BOA within 24-hours (with more time allotted as needed on a case-by-case basis) of completing both the first and second assessments and will contain a summary of the assessment data. This assessment data may be used by the provider, as he or she deems appropriate, for ongoing treatment decisions. Clinical care of patients enrolled in this study will not be video-taped. Choice of treatment modality will be one of the outcome measures; data on techniques used in treatment will be collected from study providers after every session with a study patient via the Procedures Used in Treatment Checklist. The Checklist will also be used by providers to record their study patients’ self-reported PTS and depression scores, which the providers will acquire from their AHLTA (medical record) session notes on a biweekly basis.

*8.2. Analysis Plan*

The first set of Objectives concern therapist behaviors, specifically hypothesizing that Extended Training will result in a greater proportion of PTSD patients treated with PE, use of PE with more complex patients (e.g. comorbidities). The analyses will be done using mixed effects regression models with repeated measures, incorporating as covariates baseline values on the outcome measures when available and confounded ancillary variables as needed. Planned between and within-group contrasts will be done at each assessment by t-test. The measures to address the first two objectives will be derived from self-report scales completed after consultation. When feasible, summary measures will be derived by summing items bearing on the same issue. For example, the Implementation Survey includes a 25-item section listing comorbid conditions and complicating factors. The fidelity analysis will be based on ratings by IEs of recorded sessions.

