The second set of Objectives concerns changes in therapist attitudes. The analysis model will be mixed effects regression as above, with intervention arm the primary independent variable and repeated measures at post-consultation and at two and three years. The dependent measures will be summary scores derived from the Implementation Surveys, using sums of relevant items as appropriate to operationalize therapist self-efficacy, satisfaction and expectations for change. We anticipate that changes in therapist attitudes may appear very quickly in the training process, influenced by expectations about consultation and supervision at the earliest stages and experience of training as it is received.

The third set of Objectives concern changes in patient outcomes, specifically PTSD symptom severity, other symptoms, dropout, and satisfaction with treatment. The analysis design for continuous measures based on self-report scales is simple analysis of (co)variance on post-treatment outcomes (or equivalently, change), comparing intervention arms using pre-treatment measures as covariates. If dropout data are available at the individual patient level, simple chi-square, logistic regression or generalized mixed effects models will be used to compare interventions. For all patient level outcomes, mixed models may be needed because patients are nested within therapists. Preliminary analyses will explore the need to include therapist as a random design effect to account for possible clustering effects (Crits-Christoph & Mintz, 1991). For the therapist level outcomes, the impact of baseline patient (or therapist) characteristics that are confounded with intervention condition will be evaluated using analysis of covariance.

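### The analysis plan adds covariates only when they look confounded with arm and never names installation, and no stratification of the three-installation randomisation is stated

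*Protocol*

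**What the plan says.** **Allocation.** Section 6.1 states: "Two hundred (200) mental health providers at three medium-to-large CONUS Army installations will be randomly assigned". Section 8.1 repeats this for consented providers, so the unit is the individual provider within an installation. The whole method in section 2.4 is "Participants will be randomized to conditions by a computer-based random list generator", next to the target "The study proposes to enroll approximately 100 participants in each condition". Strata, blocks and separate lists per installation are not mentioned anywhere.

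**Covariates.** For provider-level outcomes, section 8.2 plans mixed models "incorporating as covariates baseline values on the outcome measures when available and confounded ancillary variables as needed". Later in the same section, for therapist-level outcomes, the impact of baseline patient or therapist "characteristics that are confounded with intervention condition will be evaluated using analysis of covariance".

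Patient-level outcomes are adjusted for pre-treatment measures. A therapist effect is added if preliminary analyses suggest that it is needed. Section 2.2 also gives the Additional Services Form a role in controlling for concurrent services and board review. Installation is not named as a covariate in any of these places.

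**Sample size.** Sections 2.4, 5.1 and 6.1 imply about 200 providers. The opening description says "120 mental health providers will attend a 4-day PE workshop", and section 7 also lists 120 subjects. The protocol shows no power calculation.

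**The concern.** Providers were randomised, so any association between a baseline variable and arm is chance. Choosing covariates by that association has two consequences.

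- The adjusted model is settled only after the data are seen. The protocol gives no list of candidate variables and no threshold for calling one confounded.
- The criterion is the wrong one for precision. A covariate earns its place by predicting the outcome, not by being unbalanced. An installation effect on PE use would go unmodelled whenever the arms happened to be balanced across installations.

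Installation is a plausible predictor here. Workshops are held on site, PE use is optional, and each site may use its own PTSD screening tool. The protocol does not show how large any installation effect is. What is at stake is the precision of the main comparison between arms and a model fixed in advance; bias is not at stake.

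**Working it through.** The protocol gives no alpha, power, effect size or installation effect, so it has no figure to reproduce. The check below sizes the consequence.

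**Inputs from the protocol:** three installations; 1:1 allocation; N = 200 or N = 120.

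**Assumptions:** two-sided alpha 0.05; outcome SD 1; d = 0.40 at N = 200 and d = 0.515 at N = 120, each chosen to give about 80% power without an installation term; ρ, the share of outcome variance due to installation, from 0.01 to 0.10.

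**1. Cost of leaving installation out.** With n = N/2 per arm, power ≈ Φ(d·√(n/2)/σ − 1.96). Here σ = 1 without the installation term, and σ = √(1 − ρ) with it in the model and the arms balanced within installation.

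- N = 200, no term: 0.40 × √50 = 2.828; Φ(0.868) = 0.807.
- N = 200, ρ = 0.05: 2.828/√0.95 = 2.902; Φ(0.942) = 0.827.
- N = 120, no term: 0.515 × √30 = 2.821; Φ(0.861) = 0.805.
- N = 120, ρ = 0.05: 2.821/√0.95 = 2.894; Φ(0.934) = 0.825.

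| ρ | N = 200: power with term (without: 0.807) | N = 120: power with term (without: 0.805) | Unadjusted N needed to match, N/(1 − ρ) |
|---|---|---|---|
| 0.01 | 0.811 | 0.809 | 202 / 121 |
| 0.05 | 0.827 | 0.825 | 211 / 126 |
| 0.10 | 0.846 | 0.845 | 222 / 133 |

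The gain is about 0.4, 2 and 4 power points respectively.

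**2. What stratifying the list adds.** With installation in the model, the information relative to perfect balance is Σ n_s f_s(1 − f_s)/(N/4), where f_s is the fraction of the n_s providers at site s in one arm. Its average over three sites is:

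- List fixed 1:1 overall: 1 − 2/(N − 1), which is 0.990 at N = 200 and 0.983 at N = 120.
- Coin flip: 1 − 3/N, which is 0.985 and 0.975.

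The average loss is therefore 1.0–1.5% at N = 200 and 1.7–2.5% at N = 120. At ρ = 0.05, a list fixed 1:1 overall with the installation term gives power of about 0.823 and 0.819. Stratification then adds 0.4 and 0.6 points. With coin-flip allocation:

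- N = 200: Φ(2.902 × √0.985 − 1.96) = Φ(0.920) = 0.821, so stratification adds 0.6 points.
- N = 120: Φ(2.894 × √0.975 − 1.96) = Φ(0.898) = 0.815, so stratification adds 1.0 point.

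**3. How often imbalance would occur if the list is not stratified.** The table gives the chance that at least one installation splits 60:40 or worse (200,000 simulated allocations per case).

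| List type | N = 120, equal sites | N = 120, sites 50/30/20% | N = 200, equal sites | N = 200, sites 50/30/20% |
|---|---|---|---|---|
| Coin flip | 61% | 56% | 26% | 42% |
| Fixed 1:1 overall | 36% | 36% | 10% | 28% |

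The range is about 36–61% at N = 120 and 10–42% at N = 200. Visible imbalance is common, but step 2 shows that it costs little once installation is in the model.

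**The case against.** A reader might infer that the protocol prescribes one unrestricted list. It does not. A list generator can produce blocked lists or lists per site, and the target of about 100 per condition fits a list balanced 1:1. The imbalance figures therefore hold only if the list is unstratified, and they depend on its type.

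A reader might also infer an explicit rule that installation enters only if confounded. The text gives a generic rule and does not mention installation; the second statement of it, on patient or therapist characteristics, may not reach installation at all.

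Nor do the documents show that leadership support or session time differ by site. Section 7.3 makes both an inclusion criterion for every provider. Screening tools may differ, but patient eligibility rests on a common CAPS-5 threshold.

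It is also fair to say that imbalance in an individually randomised trial causes no systematic bias, and that both arms are expected at every installation. Planned adjustment for baseline values may already absorb part of an installation effect, so ρ is best read as the share left after that adjustment. All of this stands and limits the size of the point.

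The last defence is that a statistical analysis plan, not shown here, may name the covariates. That does not remove the point, because section 8.2 already fixes a selection rule and the rule is a poor one. Stratification acts at allocation, so a later analysis plan cannot add it to a list already used.

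**Conclusion.** The point holds as a weakness in the stated covariate rule, together with an unstated stratification. It is not evidence of a biased comparison. At either sample size, leaving out installation costs about 2 power points if installation explains 5% of outcome variance and about 4 points at 10%, from a start of about 80%; at 1% the cost is negligible. At 10%, the unadjusted trial would need about 22 more providers at N = 200 (222 − 200) or 13 more at N = 120 (133 − 120) to make up the loss. These figures rest on an assumed installation effect, assumed effect sizes and a normal approximation. Nearly all of the benefit comes from the model term; stratifying the list adds a small amount. A rule without candidates or threshold also leaves the main model open until the data are seen, and that holds whatever the size of ρ. The change is worth making because it costs almost nothing.

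**What to change.** **Section 8.2.** For the main contrasts, replace the clause on ancillary variables with covariates named in advance: the baseline value of the outcome (where collected) and installation as a fixed effect, in both the provider-level and the patient-level models, whatever balance is observed. If other covariates are wanted, for example from the Additional Services Form, name them in advance as well. Any adjustment prompted by observed imbalance should be labelled a sensitivity analysis.

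**Section 2.4.** State that the 1:1 list is generated in blocks separately for each installation. If lists have already been produced, state how they were made.

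**Cost.** One list per installation instead of one overall, and one three-level factor (two degrees of freedom) in each model. No extra data are needed, since the installation of every provider is known.
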